### Objectives

The overall aim of this pilot randomized controlled trial is to examine the feasibility, acceptability, and preliminary efficacy of Yoga-Sanskar (YS), a yoga-based intervention to improve antenatal depression.

The primary objectives of this pilot randomized trial are:

1. To estimate participant eligibility, recruitment and retention-in-care and study completion rates.

2. To assess the feasibility of delivering Yoga-Sanskar intervention and acceptability of this intervention by the participants.

3. To assess the adherence rate, safety, and preliminary efficacy of Yoga-Sanskar intervention in improving antenatal depression (primary outcome).

The secondary objectives of this pilot randomized trial are:

1. To assess the preliminary efficacy of Yoga-Sanskar intervention on anxiety, stress, and quality of life (secondary outcomes) during pregnancy.

2. To assess the preliminary efficacy of the intervention on pregnancy outcomes (preterm labor, type of delivery, birthweight, and post-partum depression.

3. To explore the feasibility of administering all the evaluation tools including the Client Service Receipt Inventory to assess the healthcare and intervention costs.

4. To explore the feasibility of following up recruited participants four weeks post-delivery.

5. To study the psychometric properties of the translated versions of the Pregnancy Experience Scale, Common Symptoms in Pregnancy inventory, Attitude towards Yoga during Pregnancy scale, and the Five Facet Mindfulness Questionnaire.

**
*Trial design*
**

Single-blind individual randomized parallel group-controlled pilot trial with 1:1 allocation ratio.

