Improvement in self-awareness/mindfulness is proposed as a potential mechanism of action through which a yoga-based intervention improves mental health outcomes/depression
^
13
^. The training during yoga sessions will focus on improving self-awareness/mindfulness, as the increase in mindfulness is associated with decreased distress and other psychological symptoms. We will use a 17-item Five-Facet Mindfulness Questionnaire that measures five aspects: non-reactivity to inner experience, observing, acting with awareness, describing with words, and non-judging of experience. The original English version of the scale
^
34
^ is translated into Marathi and is included in the supplementary file (
*Extended Data*
^
17
^).

**
*Pregnancy outcomes*
**

We will gather information about the outcome of pregnancy (normal birth/stillbirth), whether the delivery took place at-term, and the birthweight of newborn based on the hospital records.

**
*Self-report log*
**

Participants in both arms will document any injuries or non-serious adverse events during the trial in the yoga journal (and a similar journal will be given to the participants in the EUC arm). IC and
*Sahayoginis* will keep track of this and report to the CRC in case of adverse events.

**
*Economic evaluation*
**

In the future explanatory trial, we plan to assess the cost-effectiveness of the YS intervention relative to the EUC. Effectiveness/health outcomes will be estimated using the Quality Adjusted Life Years based on the EQ-5D-5L data collected at the baseline and three months post-randomization. Costs will comprise intervention costs, healthcare resource costs, and wage loss costs. In this pilot trial, we will explore the feasibility of using the Client Service Receipt Inventory to estimate healthcare resource costs and wage loss costs. Intervention costs will be estimated using the trial records.

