### Sample size

We plan to recruit around 25 pregnant women with depression in each arm (total=50). This is based on the recommended sample size for pilot randomized controlled trials by Whitehead
*et al.* According to the authors, a sample size of 25 in each arm is adequate for a small standardized effect size (0.2) between the two arms
^
35
^. Assuming a conservative prevalence of 10% for antenatal depression and a 15% non-response rate, we plan to screen around 600 pregnant women.

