### Oversight and monitoring

**
*Composition of the coordinating center and trial steering committee*
**

The Trial Management Group (TMG) will oversee the daily execution of the trial, while the Trial Steering Committee (TSC) will offer supervision. The TMG will include the principal investigator, research assistants (RAs), the Intervention Coordinator (IC), yoga instructors, and a representative of
*Sahayoginis*.

There will be six members in the TSC and one of them will be a woman who has recently delivered a baby. She will represent patient perspectives and ensure that the safety of the participants is prioritized throughout the implementation of the trial. Two independent researchers will co-chair TSC. Details about the membership, roles and responsibilities, and TSC meetings are provided in the supplementary file (
*Extended Data*
^
36
^). Representatives from the TMG will participate in the TSC meetings.

**
*Composition of the data monitoring committee, its role and reporting structure*
**

Due to the nature of the trial and the low risk for participants, the TSC will also take on the role of the data monitoring committee. The Clinical Research Coordinator will submit a report every two weeks summarizing SAEs in both the arms without removing the blinding. During the TSC meetings, data related to trial progress and participants' safety will be reviewed and discussed.

**
*Adverse event reporting and harms*
**

The IC and yoga instructors will be trained to identify Serious Adverse Events (SAEs) and notify them to the CRC. CRC will maintain a log of all the following SAEs in both arms.

1)Death due to any cause2)Hospitalization due to any cause3)Suicide attempt4)Spontaneous abortion or stillbirth

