RAs will independently document SAEs at the three-month and post-delivery follow-up assessment. PI will submit an initial report to the Institutional Ethics Committee about the SAE (related or unrelated) within 24 hours of becoming aware. This will be followed up by a detailed analysis report submitted to the Institutional Ethics Committee within 14 days of the knowledge of the occurrence of the SAE. A standard operating procedure will include all the details about the detection, appropriate response, and reporting of SAEs. If any SAE requires an immediate response, an independent medical specialist will do so within two working days. A summary of all serious adverse events will be sent to the Institutional Ethics Committee, the funder, and the TSC regularly as part of the progress report. If there is a statistically significant difference in prevalence of SAEs in the two arms of the trial, the TSC will take a decision to unblind the data. All necessary and appropriate medical assistance will be provided to participants in the PIMS for injuries related to participation in the trial (intervention arm). There will be no financial burden on the participants for trial-related injuries and adverse events.

**
*Frequency and plans for auditing trial conduct*
**

The sponsor and the Institutional Ethics Committee will monitor the aspects of the study on an ongoing basis. PI will send a monthly progress report to the Institutional Ethics Committee.

**
*Plans for communicating important protocol amendments to relevant parties (e.g., trial participants, ethical committees)*
**

During the progress of the trial, we may have to undertake certain modifications in the protocol that may affect the scientific value of the study, participant safety, or how the study is conducted. PI will first submit these modifications to the Institutional Ethics Committee as amendments to the protocol and then seek approval from the TSC and the sponsor. We will communicate all the changes made to the protocol to the trial participants through written communication. The final report submitted to the funder will enlist all the amendments to the protocol.

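### The stated between-arm safety trigger is an unspecified significance test that is very unlikely to fire at 25 per arm, and counting every hospital admission as an SAE weakens it further

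*Protocol article*

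**What the plan says.** All the provisions are in the protocol article, mostly under Oversight and monitoring.

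- **Trigger** (Adverse event reporting and harms): "If there is a statistically significant difference in prevalence of SAEs in the two arms of the trial, the TSC will take a decision". The decision concerns unblinding. No test, significance level or timing is attached.
- **SAE list** (same subsection): death, "Hospitalization due to any cause", suicide attempt, and spontaneous abortion or stillbirth. No exception for admission to give birth is stated.
- **Collection window** (same subsection): "RAs will independently document SAEs at the three-month and post-delivery follow-up assessment". Under Outcomes, the assessments after birth are placed four weeks after delivery.
- **Reports** (data monitoring committee): the Clinical Research Coordinator will "submit a report every two weeks summarizing SAEs in both the arms without removing the blinding". The TSC also acts as the data monitoring committee and reviews safety data at its meetings.
- **Individual reporting**: each SAE, related or not, goes to the ethics committee within 24 hours, with a detailed analysis within 14 days.
- **Size** (Sample size): "We plan to recruit around 25 pregnant women with depression in each arm (total=50").
- **Birth data** (Pregnancy outcomes): these include "the birthweight of newborn based on the hospital records". The share of women who deliver in hospital is not given.

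**The concern.** Safety is among the pilot's primary objectives, and the participants are pregnant. The one rule that compares the arms depends on statistical significance, which a 50-woman trial reaches only with an extreme split. The quantity compared is overall SAE prevalence. If routine hospital births count as SAEs, prevalence rises towards 100% in both arms and any real difference in other events is diluted.

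At stake is whether a moderate excess of serious events in one arm would prompt the look at unblinded data that the rule is meant to provide. Because no test is named, it is also unclear whether the rule has been met on a given set of counts.

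**Working it through.** The protocol gives no power, significance level or expected SAE rate for this trigger, so there is no stated figure to reproduce.

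**Inputs from the protocol.** 25 per arm (Sample size); 1:1 allocation (Trial design); SAE list and trigger (Adverse event reporting and harms); entry at 12–26 weeks (Eligibility criteria).

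**Assumptions.** Two-sided 0.05. Both Fisher's exact test and uncorrected Pearson chi-square are shown, because the protocol names chi-square only for baseline comparisons. SAE risks and the hospital-birth share h are assumed and varied. All power figures are for a single look.

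**Step 1: smallest split that triggers, 25 v 25.**

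For a v 0 events, two-sided Fisher p = 2 × C(25,a)/C(50,a).

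- a = 5: 2 × 53,130/2,118,760 = 0.0502, not significant.
- a = 6: 2 × 177,100/15,890,700 = 0.022, significant.

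For chi-square, X² = N(ad − bc)²/(product of the margins).

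- 4 v 0: 50 × (4 × 25)²/(25 × 25 × 4 × 46) = 4.35, p = 0.037, significant.
- 3 v 0: 50 × (3 × 25)²/(25 × 25 × 3 × 47) = 3.19, p = 0.074, not significant.

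With events in both arms, Fisher needs 7 v 1 (p = 0.049) or 9 v 2 (p = 0.037); chi-square needs 6 v 1 (p = 0.042) or 8 v 2 (p = 0.034). The choice of test matters: 5 v 0 does not trigger under Fisher (0.0502) but does under chi-square (0.018).

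**Step 2: chance of triggering, delivery admissions excluded.** Power is the sum, over all pairs (a, b) with p < 0.05, of Bin(a; 25, p1) × Bin(b; 25, p0).

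| SAE risk, one arm v other | Fisher | Chi-square |
|---|---|---|
| 4% v 12% | 3.5% | 16% |
| 5% v 10% | 1% | 8% |
| 5% v 20% | 20% | 38% |
| 5% v 25% | 37% | 56% |
| 5% v 40% | 82% | 91% |

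For 80% power against a 5% risk, the other arm would need about 39% (Fisher) or 34% (chi-square).

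**Step 3: effect of counting hospital births.** If a share h deliver in hospital, independently of other SAEs, then P(any SAE) = 1 − (1 − h)(1 − p). For a true 5% v 40% difference in other SAEs:

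| h | Prevalence by arm | Fisher | Chi-square |
|---|---|---|---|
| births not counted | 5% v 40% | 82% | 91% |
| 50% | 52.5% v 70% | 18% | 27% |
| 80% | 81% v 88% | 5% | 11% |
| 90% | 90.5% v 94% | 1% | 6% |
| 100% | 100% v 100% | 0% | 0% |

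For example, at h = 0.9: 1 − 0.1 × 0.95 = 0.905 and 1 − 0.1 × 0.60 = 0.94.

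**Step 4: when the dilution applies.** Entry at 12–26 weeks plus about 13 weeks puts the three-month visit at about 25–39 weeks. Most events up to then are therefore undiluted. The loss in Step 3 builds up as women deliver and is complete only once all have done so.

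**The case against.** The strongest reply is that this is one element of a wider safety system. The text says what happens if there is a significant difference; it does not say that the TSC may act only then. Every SAE reaches the ethics committee individually, deaths, pregnancy losses and suicide attempts are separate items on the list, the TSC reviews safety, and yoga-related events are unblinded to the obstetrician. All of this stands. A reader might infer that real events would be buried or that the TSC could not act otherwise, and the document supports neither. Still, none of these provisions is a stated between-arm comparison with an action attached.

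A second reply is that the trigger can be met. That is right: it is insensitive, and impossible to meet only in the limit where every woman has an SAE because every birth counts.

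A third is that a standard operating procedure, not shown, holds the SAE details and may exempt delivery admissions. It may, but the list in the protocol covers hospitalisation from any cause, and such an exemption would have to be squared with it.

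Two further readings are tempting but unsupported. A reader might infer that the blinded Research Assistants and the Intervention Coordinator attend the TSC. The text says only "Representatives from the TMG will participate in the TSC meetings", without saying which, and the terms of reference are not shown. A reader might also infer that a test is repeated every fortnight. Reports are fortnightly; no schedule of tests is stated, and repeated looks would raise the chance of triggering.

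**Conclusion.** The concern holds in a limited form. The protocol fixes a between-arm rule that is very unlikely to fire for any moderate excess of SAEs: 20% (Fisher) or 38% (chi-square) for a fourfold rise from 5% to 20%. Read literally, its own SAE definition then removes most of the remaining sensitivity as women deliver. The two provisions work against each other.

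The size rests on assumptions the protocol does not settle: two-sided 0.05, the choice of test, the SAE risks, and a hospital-birth share for which 50% to 100% is shown. The direction is the same under both tests and across that range. Because case-by-case reporting and TSC review continue, this is a worthwhile and cheap correction to the wording of the safety rule, not a failure of safety oversight as a whole.

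**What to change.** 1. Under Adverse event reporting and harms, remove statistical significance as the condition. State that the TSC reviews SAE counts by coded arm and by type (death, pregnancy loss or stillbirth, suicide attempt, hospitalisation) and may decide to unblind on its judgement, whatever the p-value.
2. Reconcile the SAE list with the post-delivery collection window, so that admissions for routine delivery are identified separately and do not enter the between-arm comparison. The sponsor and TSC should decide the definition, and the standard operating procedure should match it.

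The cost is wording in the protocol and, where needed, in the SAE form, the operating procedure and the TSC terms of reference. No extra participants are needed. The downside is that TSC members would see counts by coded arm.

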### Dissemination plans

Our research will primarily communicate key findings through publications in open-access peer-reviewed journals. Upon acceptance for publication, the final peer-reviewed journal manuscripts resulting from this research will be archived in PubMed Central (or an equivalent digital repository). PI and other study team members will present research data at national and international scientific conferences, including oral presentations, posters, and published abstracts, prior to formal publication. Comprehensive study reports containing result interpretations and recommendations will be shared with all major stakeholders. Findings will also be disseminated to participating communities through leaflets, flyers, local media, and interactive community meetings.

## Discussion

In this protocol paper, we provide the rationale, detailed description (using the TiDieR guidelines), and evaluation plan for assessing the feasibility, accessibility, and preliminary efficacy of Yoga-Sanskar, a yoga-based intervention for antenatal depression. Almost all studies evaluating the effect of yoga on depression during pregnancy have taken place either in high-income settings such as the United States and the United Kingdom or in urban settings in India
^
7
^. We need to understand more about women's uptake of yoga-based intervention in rural India. Previous trials have yet to undertake an economic evaluation of yoga-based intervention, and there is no data about the costs involved in the delivery/practice of the intervention. This pilot randomized controlled trial tries to address these critical research gaps.

We will recruit participants from the hospital setting (antenatal clinic of PIMS and antenatal clinics run by private obstetricians) and community settings. The latter's advantage is that women get more time to interact with the study team. This facilitates their decision to participate in the study compared to the hospital setting where they are more concerned about the delays in antenatal check-up due to interaction with the study team members. On the other hand, it is easier to approach a large number of pregnant women on a single day in hospital setting. We will screen all pregnant women for the current episode of depression, generalized anxiety disorder, and perceived stress. Thus, even if a pregnant woman is enrolled in the comparison arm of the study or is not eligible to participate in the study, she will at least get an assessment of her mental health status and a single health education session. Information related to sleep hygiene, diet, and physical activity will be delivered in this single health education session of about ten minutes using an educational leaflet. In a rural setting, the most critical challenge for a pregnant woman is to travel to any location far from her house to participate in any behavioral intervention. She also finds it difficult to take time out of her daily routine to practice these interventions. These were the key findings from our previous trial in the same geographical setting
^
37
^ and our formative research. Yoga-Sanskar intervention is designed in a way that the time commitment for enrolled women to attend supervised group yoga sessions is limited to three sessions, about five hours of their time outside the home. After completing these three sessions that constitute the LEARN phase, we will provide them with a journal and access to YouTube recordings to enable regular home practice of yoga. Yoga-instructors and
*Sahayoginis* will regularly contact and motivate the participants to continue home practice. We are hopeful that these strategies will improve the adherence to the intervention and will have a positive effect on the outcomes. At the end of the LEARN phase, we will assess the competency of the participants to practice yoga independently and safely. This is a unique feature of our study as previous studies evaluating yoga-based intervention in pregnant women have not included competency assessment
^
7
^.

During the conduct of the trial, we will be cautious to ensure the safety of the participants. As noted earlier, who will recruit only those women who do not have history of spontaneous abortion, each supervised yoga session will begin with completion of the safety checklist, and the project team will keep a track of injuries documented by the participants every week.

A community representative and a yoga instructor have reviewed this manuscript and have agreed to be one of the co-authors. The protocol was also presented to all
*Sahayoginis*, and their feedback has been incorporated.

Overall, this study will address an important research gap in the field of perinatal mental health and will set the stage for undertaking the explanatory trial.

## Ethics and consent

The Institutional Ethics Committee of the Pravara Institute of Medical Sciences (Approval Number: PIMS/DR/RMC/477) approved this study. Eligible participants who express willingness to participate in the study will provide informed written consent by completing a hard copy of the consent form.

## Data Availability

No data are associated with this article. Figshare: Participant Information Sheet.
https://doi.org/10.6084/m9.figshare.25866205
^
38
^. Figshare: Informed Consent forms.
https://doi.org/10.6084/m9.figshare.25867051
^
10
^. Figshare: Assessment Tools.
https://doi.org/10.6084/m9.figshare.25866424
^
17
^. Figshare: Trial Steering Committee_Terms of Reference.
https://doi.org/10.6084/m9.figshare.25866523
^
36
^. Data are available under the terms of the
Creative Commons Attribution 4.0 International license (CC-BY 4.0). Figshare: SPIRIT checklist for ‘Yoga-based lifestyle intervention for Antenatal Depression (YOGA-D): study protocol for a pilot randomized controlled trial’.
https://doi.org/10.6084/m9.figshare.25866463
^
9
^ Data are available under the terms of the
Creative Commons Attribution 4.0 International license (CC-BY 4.0).
